## *Expect With Me* group prenatal care

*Expect With Me* group prenatal care was designed based on: (1) principles of group care [35]; (2) evidence from randomized controlled trials demonstrating improved birth outcomes for women receiving prenatal care in a group format [18, 21]; (3) clinical guidelines for prenatal care delivery [36]; and (4) research on patient and provider engagement through social media and technology [37–39]. Designed with national dissemination as a primary consideration, *Expect With Me* incorporates the best evidence-based aspects of existing models of group care [22, 40–42] with a novel IT platform to improve patient engagement and support, enhance health behaviors and decision making, connect providers and patients, and improve health service delivery.

*Expect With Me* provides care to groups of 8–12 women of the same gestational age. Women receiving *Expect With Me* begin prenatal care in the traditional manner. Formal intake (history, exam) is performed at an initial visit prior to group assignment. All prenatal care thereafter occurs within a group setting, except for health issues that require privacy and cervical assessments in late pregnancy. Ultrasounds and laboratory screenings occur per ACOG clinical guidelines [36]. *Expect With Me* is implemented from week 14 of pregnancy (after initial individual assessment) through delivery, following the same schedule as individual care. However, group visits are 90–120 min each, and follow a unique structured curriculum that incorporates the standard content of prenatal care, and emphasizes critical contemporary health issues relevant to pregnancy, such as nutrition, physical activity, stress/mental health, and sexual health. Table 1 summarizes the timing and recommended topics to be covered during each session. Participants may bring their partner, family member, or other support person to group sessions.

**Table 1 Tab1:** *Expect With Me* group prenatal care session timing and topics

Session	Themes	Topics
1 (13–17 weeks)	You’re a healthy mom	• Eat and live healthy for you and your baby • Stay active while you’re expecting • Maintain healthy weight during pregnancy • Understand routine prenatal testing and emergencies • Know what blood pressure and weight numbers are healthy for you

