## Organizations and study population

Beginning February 2014, *Expect With Me* was implemented in five clinical sites in Nashville TN, Detroit MI, and McAllen TX. Each site receives financial and advisory assistance to support the implementation and evaluation process. Yale and UnitedHealth Group recruited clinical sites. An important goal was to include sites located across different regions with different target populations. Interested sites completed a site eligibility form/site profile. If an organization met criteria to participate, a site visit was conducted by the research team to discuss the program procedures and requirements for participation in the study in more detail. The inclusion criteria for health care organizations was as follows: sufficient obstetric patient volume to meet study recruitment goals; support within the institution to integrate group prenatal care into practice; willingness to implement *Expect With Me* according to protocol during the study period; participation in the evaluation study data collection activities; and intention to continue *Expect With Me* after the project period.

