## Analyses

Descriptive analyses of quantitative data will be performed. Women who participated in group prenatal care and those who received individual care will be matched on the basis of propensity scores. Propensity score matching is a statistical technique to correct for observable difference between the treated and non-treated group, thereby reducing selection bias and strengthening causal inferences, in observational studies [60]. We will use multiple imputation and maximum likelihood techniques to handle missing data and sensitivity analyses to assess the robustness of inferences about treatment effects to various missing data assumptions, as needed.

Generalized linear and logistic regression models will be used to analyze continuous (e.g., gestational age at delivery and birth weight) and dichotomous outcomes (e.g., preterm birth, low birth weight), respectively. Negative binomial regression models will be used to analyze count outcomes (e.g., neonatal intensive care unit days). Each model will include a main effect for treatment group (*Expect With Me* vs. individual care). Because many women who attend group prenatal care sessions also supplement with individual visits [61], adjusted models will control for number of individual visits, as well as contain predictor variables that are clinically meaningful to a specific hypothesis of interest.

Trajectories of change for outcomes that are repeatedly measured over time (e.g., weight) will be examined using linear and non-linear mixed effects modeling, with a random effect for subject. An optimal covariance structure will be selected based on the likelihood ratio test for nested models and based on the Akaike Information Criterion for non-nested models [62]. The main independent effects of time, treatment, and second-degree interactions of these predictors will be considered in each model, adjusting for other covariates as described above.

Multilevel mixed models will be used to identify factors that influence primary outcomes among *Expect With Me* patients, with the effect of site modeled as a random effect. A scale variable that will reflect a woman’s attendance level at prenatal care group visits will be created to evaluate whether there is a “dose–response” intervention effect. Structural equation models will be used to examine factors that may mediate the relationship between participation in group care sessions and improved outcomes.

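### No outcome or cost model includes the prenatal group in which Expect With Me care is shared, so intervals will be too narrow if outcomes correlate within groups

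*Protocol article*

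**What the plan says.** The section on Expect With Me group prenatal care states that the programme "provides care to groups of 8–12 women of the same gestational age". After an individual intake visit, "All prenatal care thereafter occurs within a group setting", with exceptions for private health issues and late cervical checks. Comparison women receive individual care at the same sites.

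The Analyses section then sets out three kinds of model:

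- **Between-arm models.** "Generalized linear and logistic regression models will be used to analyze continuous" and dichotomous outcomes, with negative binomial models for counts. "Each model will include a main effect for treatment group". Adjusted versions add the number of individual visits and clinically relevant predictors.
- **Trajectory models.** These use "linear and non-linear mixed effects modeling, with a random effect for subject".
- **Intervention-only models.** A multilevel analysis, fitted to women in the programme alone, looks for predictors of the primary outcomes. Its only named random level is the clinic: "with the effect of site modeled as a random effect". The Organizations and study population section says that the programme "was implemented in five clinical sites in Nashville TN, Detroit MI, and McAllen TX".

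The Cost analyses section plans ordinary least squares, confirmed by a gamma model with log link, and mentions no clustering. The Sample size section mentions no intraclass correlation or design effect.

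**The concern.** Women in the same prenatal group share facilitators, sessions and peers for most of pregnancy. The article's own theory, in the section on development of the programme, is that groups work through mutual support and new shared norms. Correlation of outcomes within a group is therefore something the design expects. Individual-care women have no such grouping, so the design is partially nested: about 83 to 125 groups in one arm (1,000/12 to 1,000/8) and none in the other.

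A model that ignores this treats the intervention arm as carrying more independent information than it does. Confidence intervals for the between-arm contrast would be too narrow and the test would reject too often. The effect is larger in the intervention-only model for any predictor that varies by group, such as facilitator or content delivered, because such predictors bear the full design effect.

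**Working it through.** **Inputs from the article.** Group size 8–12; 2:1 matching; about 900 of 1,000 Expect With Me women followed; control preterm rate 9.6%; relative reduction 33% (lower end of 33–34%); alpha 0.05, one-tailed; target power 0.80.

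**Inputs assumed.** Intraclass correlation (ICC) 0.01–0.05, since none is given; 10 women per group; 1,800 controls (2 × 900).

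**Step 1: the plan's own figure.** With rates 0.096 and 0.096 × 0.67 = 0.06432, pooled variance, no continuity correction and independent women, a two-sided 5% test at 80% power and 2:1 allocation needs 1,768 controls and 884 Expect With Me women. This matches the article's pair of numbers exactly with a design effect of 1, so clustering was not allowed for. (The article labels the test one-tailed and 1,768 the total. Under those labels the calculation gives 1,387 + 694 = 2,081. That mismatch is a separate matter.)

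**Step 2: design effect, intervention arm only.** DE = 1 + (m − 1) × ICC. With m = 10: 1 + 9 × 0.01 = 1.09; 1 + 9 × 0.02 = 1.18; 1 + 9 × 0.05 = 1.45.

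**Step 3: standard error of the contrast.** Ratio of true to naive = √[(1/1800 + DE/900) / (1/1800 + 1/900)] = √[(1 + 2·DE)/3]. For DE = 1.09 this is √1.06 = 1.03; for DE = 1.45 it is √1.30 = 1.14.

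**Step 4: type I error.** One-sided: 1 − Φ(1.645/ratio). Two-sided: 2 × [1 − Φ(1.960/ratio)].

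**Step 5: power of a correct one-sided analysis.** Φ[(0.03168 − 1.645·SE₀)/SE₁], where SE₀² = 0.08544 × 0.91456 × (1/1800 + DE/900) and SE₁² = 0.096 × 0.904/1800 + DE × 0.06432 × 0.93568/900.

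| ICC | DE | SE ratio, contrast | Error, one-sided | Error, two-sided | One-sided power |
|---|---|---|---|---|---|
| 0 | 1.00 | 1.00 | 0.050 | 0.050 | 0.886 |
| 0.01 | 1.09 | 1.03 | 0.055 | 0.057 | 0.869 |
| 0.02 | 1.18 | 1.06 | 0.060 | 0.064 | 0.853 |
| 0.05 | 1.45 | 1.14 | 0.075 | 0.086 | 0.803 |

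**Sensitivity to group size.** For m = 8 to 12, the SE ratio is 1.02–1.04 at ICC 0.01 and 1.11–1.17 at ICC 0.05. One-sided power at ICC 0.05 is 0.821 (m = 8) to 0.785 (m = 12).

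**Step 6: group-level predictors in the intervention-only model.** The ratio is √DE: √1.09 = 1.04 to √1.45 = 1.20.

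**Step 7: what the ICC range means for preterm birth.** The standard deviation of true group risks is √[ICC × p(1 − p)] with p = 0.06432. At ICC 0.01 this is √(0.01 × 0.0602) = 0.025; at ICC 0.05 it is √(0.05 × 0.0602) = 0.055. A spread of 5.5 percentage points around a mean of 6.4% is large, so the low end is more plausible for this outcome.

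**The case against.** The strongest reply is that the article condenses a fuller plan. It names model families and a treatment term, never says that women are treated as independent, and may leave the variance estimator to a document not shown. That would settle the matter if the article were silent on dependence, but it is not. It names subject and site as random effects and omits the level that the intervention itself creates. The promise to select a covariance structure belongs to the repeated-measures models and does not supply a group level. The point survives as a gap in what is specified.

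Three stronger readings are tempting, and the documents do not support them.

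- **That the standard errors are too small as a matter of fact.** This needs a positive ICC, and none is given. The comparison is also propensity-matched 2:1. Ignoring positive correlation within matched sets works in the opposite direction, so the net effect depends on how matching is handled.
- **That the study is underpowered because of clustering.** Two-sided power does fall from 0.81 to 0.78–0.70, but the article states a one-tailed test. On that test, at 900 + 1,800 with 10 per group, power stays at or above 0.80 across the assumed range. It dips below (0.785) only with groups of 12 at ICC 0.05.
- **That a random site effect with five sites is an error.** Five levels estimate a variance imprecisely, but that variance is not the target of the intervention-only model. Fixed or random site is a modelling preference. Only the missing group level is substantive.

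**Conclusion.** The point holds in conditional form. The prenatal group appears in none of the between-arm, trajectory, intervention-only or cost models. If outcomes are positively correlated within groups, other things equal, analyses run as written understate uncertainty. At an assumed ICC of 0.01–0.05, the contrast standard error should be about 1.03–1.14 times the naive value, and the one-sided 5% test has 5.5–7.5% error (two-sided 5.7–8.6%). For group-level predictors among Expect With Me patients the factor is about 1.04–1.20.

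For preterm birth the effect is probably near the lower figures. It may be larger for behavioural and psychosocial secondary outcomes such as breastfeeding and depression, where shared norms act more directly. These sizes rest on the assumed ICC, on 10 women per group, on uncorrelated controls and on no offset from matching. The stated power of 0.80 is not contradicted on this ground. The change should be made, but the primary comparison is unlikely to turn on it.

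**What to change.** State in the Analyses and Cost analyses sections that:

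1. Every Expect With Me versus individual-care model, including the cost regressions, uses cluster-robust standard errors with prenatal group as the cluster. The alternative is a group random intercept in the Expect With Me arm only, with individual-care women as singletons.
2. Whichever is chosen is compatible with the 2:1 matching. One option, if controls are matched without replacement, is to place each control in the cluster of the woman she is matched to, so that matched sets sit inside group clusters.
3. The trajectory models add a prenatal-group random intercept for the Expect With Me arm, alongside the subject effect.
4. The intervention-only multilevel model adds a prenatal-group random intercept. Site may stay random or become fixed.

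The cost is wording and slightly wider intervals. No new data should be needed: the online tracking system already holds composition and attendance for every group, and the process evaluation documents each patient's session attendance. If the correlation proves close to zero, the results will hardly change.

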*Expect With Me* was designed using a human-centered design approach. Human-centered design is an iterative and participatory process to help ensure innovations are acceptable, usable, and meet the needs of users [47]. This approach has been used to shape healthcare to meet the multiple levels of need of clinicians and patient populations [48–51]. A series of key informant interviews with twenty prenatal care stakeholders and observational data collection during prenatal care visits were conducted, from which two important findings emerged. First, the healthcare industry historically has defined prenatal care in medical terms, and an important value proposition of group prenatal care is that it provides a context in which other basic, safety, and social needs can be addressed. Second, pregnancy provides an opportunity to re-evaluate how those needs are being met, and prenatal care messaging would benefit by moving from a frame of fear and avoidance (e.g., what not to eat, drink, and do) to embracing good health habits for women and their families. An independent team of four curriculum development and writing professionals were commissioned and—following clinical guidelines from the American Congress of Obstetricians and Gynecologists and best practices for group facilitation—developed a ten-session structured curriculum and supplemental materials for the IT platform, grounded in the lessons learned during this process. To ensure accuracy, relevance, and feasibility, all content associated with *Expect With Me* (e.g., facilitator and patient handbooks, tip sheets and other resources) was reviewed by a medical team, including obstetricians/maternal-fetal medicine specialists, midwives, and pediatricians). A pilot study of *Expect With Me* was conducted with 243 pregnant women in Nashville TN; based on this pilot, revisions were made to enhance structure and content of the curriculum. The result of this extensive formative research is a supportive, comprehensive model of group prenatal care that aims to identify and address the full spectrum of pregnant women’s needs throughout pregnancy and beyond, fostering long-term health for women and their families.

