## Methods/Design

*Expect With Me* is being evaluated via a multisite, longitudinal matched-cohort study, in which data are collected in a real-world settings at the patient and organizational levels. For national scale-up and sustainability, it is essential that the program not only be effective for patients but that the implementation strategy fits with the context of health clinics providing prenatal care [52]. A rigorous multi-method evaluation is being conducted to examine the impact of *Expect With Me* on maternal health and birth outcomes and identify and address barriers to national scalability. Cost analyses are also planned.

The study includes a rigorous process and outcome evaluation. Birth outcomes are the primary study outcomes (e.g., preterm birth, birthweight, neonatal intensive care unit admission/duration). Maternal psychosocial, health behaviors, and health outcomes (e.g., depression, breastfeeding, postpartum weight loss) are secondary outcomes.

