## Sample size

Results from previous randomized controlled trials suggest that group prenatal reduces likelihood of delivering a preterm or small for gestational age baby by 33–34% [18, 21]. Based on these findings and the national preterm birth rate of 9.6% [4], we need a minimum of 1,768 study participants with one-third (*n* = 884) receiving group prenatal care to have power of .80 to detect differences at alpha = 0.05 with a one-tailed test. With a potential 10% drop out rate due to miscarriage, pregnancy complications and changes in life circumstances (e.g., geographic move), we will recruit 1,000 women, expecting to follow more than 900 of them through one-year postpartum. We will compare primary maternal health and birth outcomes for these women with a 2–1 matched cohort of 2,000 patients receiving individual care. Therefore, the total study sample of women receiving both group and individual prenatal care will include a total of 3,000 women.

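### Controlling for number of individual visits in the between-arm models conditions on a post-treatment count tied to arm and to delivery date, and biases the adjusted estimates in a direction the documents cannot fix

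*Protocol article*

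**What the plan says.** The Analyses section sets out linear, logistic and negative binomial models for gestational age, birth weight, preterm birth, low birth weight and neonatal intensive care days. It then states: "Each model will include a main effect for treatment group". The next sentence says that "adjusted models will control for number of individual visits", on the ground that "many women who attend group prenatal care sessions also supplement with individual visits". It does not define the count for women in individual care, limit it to the group arm or relate it to length of gestation.

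The section describing Expect With Me says of care after intake: "All prenatal care thereafter occurs within a group setting, except for health issues that require privacy and cervical assessments in late pregnancy". Group care runs "through delivery, following the same schedule as individual care". Table 1 places the ninth and tenth sessions at 35–39 and 37+ weeks. The Methods/Design section names preterm birth, birth weight and neonatal intensive care admission or duration among the primary outcomes.

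**The concern.** The visit count fails as an adjustment variable on two grounds.

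- **It follows from the exposure.** A woman in group care has routine individual visits replaced by sessions; a woman in individual care has all her visits individually. Equal counts pair an ordinary group-care woman with an unusual individual-care woman.
- **It depends on the outcome.** Visits stop at delivery, so preterm birth lowers the count. Complications may lead to extra individual visits, which raises it.

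The treatment coefficient in such a model does not estimate the effect of Expect With Me as delivered. At stake are the adjusted results for the outcomes on which the study is judged. A larger sample does not remove the bias, and it can swamp the 33–34% reduction for which the study is sized.

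**Working it through.** The article gives no figure for this adjustment, so there is none to reproduce. The check asks what the adjustment does when the true effect is known.

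**Inputs from the article.** Preterm rate 9.6% and two individual-care women per group-care woman (Sample size); ten sessions (Table 1); same schedule in both arms, through delivery.

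**Assumptions not in the article.** Visits at the Table 1 midpoints (15, 19, 22.5, 27, 29, 31, 33, 35 and 37 weeks, the last at 38.5); one intake visit; 90% attendance; a mean of 1 to 5 supplementary individual visits in group care, accrued in proportion to (delivery week − 14)/25.5; an assumed gestational-age distribution; individual visits for problems in preterm pregnancies multiplied by 1 to 3 in both arms.

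**Step 1: the count tracks delivery, unequally by arm.** Take delivery at 34 against 39 weeks, two supplementary visits and no extra visits for complications.

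- Individual care: 1 + 0.9 × 7 = 7.3 against 1 + 0.9 × 10 = 10.0.
- Group care: 1 + 2 × 20/25.5 = 2.6 against 1 + 2 × 25/25.5 = 3.0.

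**Step 2: who is compared with whom.** Take a group-care woman with four individual visits. An individual-care woman with four visits has intake plus three. If all ten visits fell before delivery, the chance of attending exactly three is 120 × 0.9³ × 0.1⁷ = 0.0000087. If she delivered at 28 weeks, with four visits passed, it is 4 × 0.9³ × 0.1 = 0.29. Equal counts therefore select early deliveries in the individual-care arm.

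**Step 3: simulated odds ratio for preterm birth, no true effect** (200,000 women per setting, logistic regression).

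| Multiplier in preterm pregnancies | Mean supplementary visits | Mean individual visits, group v individual | OR, arm only | OR, adjusted for all individual visits | OR, adjusted for supplementary visits only |
|---|---|---|---|---|---|
| 1 | 2 | 2.94 v 10.03 | 1.03 | 0.0008 | 1.54 |
| 1 | 5 | 5.86 v 10.02 | 0.99 | 0.023 | 2.52 |
| 1.5 | 2 | 3.01 v 10.10 | 1.00 | 0.019 | 0.64 |
| 1.5 | 5 | 6.04 v 10.21 | 1.01 | 0.82 | 0.34 |
| 2 | 2 | 3.09 v 10.18 | 0.99 | 0.28 | 0.28 |
| 2 | 5 | 6.23 v 10.41 | 0.98 | 5.0 | 0.05 |
| 3 | 2 | 3.24 v 10.33 | 0.98 | 20.8 | 0.06 |
| 3 | 5 | 6.61 v 10.78 | 1.01 | 19.9 | 0.002 |

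With multiplier 1 and one supplementary visit, the odds ratio adjusted for all individual visits was 0.0001.

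**Step 4: hand check.** Approximately, log OR(adjusted) = log OR(arm only) − b × (mean visits in group − mean visits in individual care), where b is the log odds ratio per visit. With two supplementary visits and multiplier 1, the odds ratio per visit was 0.354, so b = −1.04. The shift is −(−1.04) × (2.94 − 10.03) = −7.4, and exp(−7.4) = 0.0006, close to the simulated 0.0008. The formula also shows why the sign can flip. Where truncation dominates, more visits go with fewer preterm births, b is negative and the odds ratio falls below 1. Where complications add enough visits, b is positive and it rises above 1.

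**Step 5: with a true 33% reduction.** The true odds ratio is (0.0643/0.9357)/(0.096/0.904) = 0.65. Arm-only estimates were 0.63 to 0.66. In the eight settings above, those adjusted for all individual visits ran from 0.0002 to 13.6.

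**Step 6: trial size.** With 3,000 women, no true effect, five supplementary visits and multiplier 1, the adjusted model rejected in favour of group care in 100% of 300 runs at one-sided 0.05. Without the count the figure was 3%. This is one scenario only.

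**The case against.** Several points on the other side are sound.

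- **Direction.** A reader might infer that the adjustment manufactures a large false benefit. That follows only if truncation at delivery is the sole link between count and outcome. Separate simulations with 900 against 1,800 women gave odds ratios of 0.002 to 0.16 under truncation alone, about 2 to 5 with roughly two extra visits in preterm pregnancies, and above that with three. The article gives no visit data, so neither sign can be claimed.
- **Definition.** The stated reason concerns group-care women who add individual visits, so the count could mean supplementary visits only, with zero in individual care. The comparison in Step 2 then does not apply. Bias still arises in most settings, as the last column of the table shows, though it passes through zero between multipliers 1 and 1.5.
- **Status of the model.** A reader might infer that the study's primary estimate is affected. The article does not say whether an adjusted or an unadjusted model is primary, and a propensity-matched comparison without this term is compatible with its text. The point concerns the adjusted estimates for the primary outcomes.
- **Collinearity.** A reader might infer that the count almost defines the arm. The article says many group-care women have individual visits. With multiplier 1, the correlation of arm with count fell from −0.94 to −0.73 as supplementary visits rose from one to five, and the variance inflation factor, 1/(1 − r²), fell from 8.2 to about 2.2. Collinearity widens intervals; it is not the source of the bias.

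Wanting to separate group sessions from added individual visits is reasonable. It is a different question from the effect of the programme as delivered, and entering the count as a covariate answers neither. Nor is this a detail left to an unseen analysis plan: the article states the adjustment outright.

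**Conclusion.** The point holds in this form: the article commits its adjusted between-arm models to a post-treatment count that is strongly tied to arm and linked to the timing of delivery. That the count is post-treatment and ends at delivery follows from the article's own text. The figures rest on the assumed attendance, supplementation, gestational-age shape and complication visits. They show that the bias can be very large in either direction and may nearly cancel in particular settings, as with the 0.82 in Step 3. They do not predict what this study would find. Removing the count restored estimates near the truth throughout the simulations, which contained no baseline confounding. The change should be made before the adjusted models are relied on.

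**What to change.** In the Analyses section, replace the sentence on individual visits with wording such as:

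> Models comparing Expect With Me with individual care will adjust only for variables fixed at or before enrolment, such as the matching variables, clinical site and baseline risk factors. Number of individual visits will not enter these models.

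Report individual visits descriptively by arm under fidelity, where the process evaluation already plans to record the share of visits held in group. If their role is of interest, examine it in the dose-response or mediation analyses that the article already plans, with allowance for gestational time at risk, for example by relating visits to those scheduled before delivery. Those analyses should also say how the count is defined in each arm.

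The cost is a sentence or two of wording. No new data are needed. The between-arm models would no longer claim to isolate group sessions from added individual visits, a separation the present term does not achieve.
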